### **9.1.1 Informed Consent Visit / Screening and baseline (Day -30 to Day -1)**

The subject will be fully informed of all study procedures and implications both verbally and in writing via use of an informed consent form. Once a subject has signed the informed consent form, a subject number (identifier) will be assigned.

Within 30 days prior to the administration of the first dose of study medication, the following procedures and assessments must be completed, and all inclusion and exclusion criteria must be met.

- Obtain informed consent
- Check of inclusion and exclusion criteria, including confirmation of BCC or SCC via histology AND confirmed by clinician review
- Target lesion(s) dimensions including depth of lesion
- Demographic data
- Baseline Modified Visual RECIST (dimensions only)
- QoL Questionnaire (via App or via eCRF or paper for subjects with no phone)
- Medical history
- Relevant concomitant medication
- Photographs of lesions to be treated are taken at the site and uploaded to the eCRF (if a medical photographer is available this is preferable)

The investigator will review all information obtained from the screening procedures. Screening failures, i.e., screened subjects not in compliance with all criteria, are to be excluded and the reason will be recorded. Subjects who fulfil all the inclusion criteria and none of the exclusion criteria will be eligible to participate in the study. Information of subject's study participation can be provided to the subject's general practitioner upon request, provided the subject has given consent for this to occur and this consent is documented in the source notes accordingly.

### **9.1.2 Treatment Period**

#### **9.1.2.1 Day 0**

- On day 0 the subject will receive treatment with Rhenium-SCT for their lesion(s). Any AEs are recorded, as well as relevant concomitant medications.
- Urine pregnancy test (females of child-bearing potential)

#### **9.1.2.2 Day 14**

14 days after the subject receives treatment, they are to enter questionnaire responses of their treatment into the subject trial App. For subjects who don't have a smart phone, this is recorded in the eCRF at the visit using a short questionnaire (see Appendix 4).

Photography is conducted at the site and images loaded to the eCRF. If a medical photographer is available this is favoured, however the site can use an available digital camera.

### **9.1.2.3 Day 30 Phone call**

On day 30, post treatment, the site will call the subject as this forms the end of the AE reported period. After this time, only AEs deemed related to treatment will be collected. During the call any AEs are to be recorded into the eCRF.

### **9.1.3 Follow-up**

Each month following the 14-day site follow-up visit, subjects who have a smart phone will be prompted via the trial App to take 2 photos of each lesion treated (one is taken in indoor light and one in natural light).

Site Follow up visits will occur at 14 days, 3 months, 6 months, 12 months and then 24 months.

#### **3 month follow up visit:**

- Concomitant medications
- Photography of treated lesions (medical photographer or site digital camera)
- CTCAE grading (see protocol appendix 1)
- AEs

#### **6 month follow up visit:**

- Concomitant medications
- Photography of treated lesions (medical photographer or site digital camera)
- CTCAE grading
- AEs
- QOL questionnaire completed via trial App or on paper during the visit if subject does not have a smart phone
- Modified Visual RECIST assessment

#### **12 month follow up visit:**

- Photography of treated lesions (medical photographer or site digital camera)
- CTCAE grading
- Quality of Life questionnaire completed via trial App (or on paper during the visit if subject does not have a smart phone)
- Cosmetic outcome; subject rated. To be completed on Trial app (or directly into the eCRF if the subject does not have a smart phone). VAS image found in the protocol appendix 3
- Cosmetic outcome: Clinician rated. To be completed into the eCRF using VAS in the protocol appendix 3
- Modified Visual RECIST assessment. Guide to assessment is found in protocol appendix 5
- Histology to be performed if lesion is visible, suspected or if this is the site's regular clinical practice

**24 month follow up visit:**

- Photography of treated lesions (medical photographer or site digital camera)
  - CTCAE grading. Grading can be found in protocol appendix 1
  - Cosmetic outcome; subject rated. To be completed on Trial app (or directly into the eCRF if subject does not have a smart phone). VAS image found in the protocol appendix 3
  - Cosmetic outcome: Clinician rated. To be completed into the eCRF using VAS in the protocol appendix 3
  - Modified Visual RECIST assessment. Guide to assessment is found in protocol appendix 5
- 
- Histology to be performed if lesion is visible, suspected or is the site's regular clinical practice
  - General review for wound complications and radiation changes. Radiation changes at months 24 are to be recorded as the CTCAE grading in protocol appendix 1, **excluding** Radiation dermatitis.

**9.1.4 Premature Study Termination**

In case of premature termination during the follow-up period, the investigator shall endeavour to arrange a premature end of study visit and perform examinations according to end of treatment visit. If the subject does not enter the follow-up period, this is the study termination (end of study) visit.

The last follow up visit (24 months) is the regular study termination visit.

The subject will leave the study if:

- they require alternative or further treatments for their lesions; or
- if they have progressive disease (PD).

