**Primary endpoint:**

- The number and percentage of lesions achieving CR during the study

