### **5.2 Primary Endpoint**

- To assess the number and percentage of lesions achieving CR during the study

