## **6. STUDY DESIGN**

### **6.1 Overall Study Design**

This is a prospective, multicentre, single arm, open-label, phase IV/ Post Marketing Clinical Follow-up (PMCF), study consisting of:

- A screening period of up to 30 days duration, to ensure that the subject is eligible for the study
- A follow-up period of 24 months. Each subject will remain in the study for 24 months from the time of their treatment with Rhenium-SCT. Subjects requiring further or alternative treatments for the target lesions during the trial period, will leave the study.

The study is completed with the last visit of last subject.

Details on all study visits can be found in the time and events schedule in Section 9.

An interim analysis is planned once 50% of subjects have recorded a 6-month follow-up visit.

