### 7.1 Inclusion Criteria

Subjects meeting the following criteria will be considered for inclusion into the study:

1. Stage I or II BCC or SCC (SCC Well to Moderately Differentiated), and clinically node negative disease
2. Confirmed Histology, and with depth of lesion noted
3. Subjects with up to 3 lesions suitable to enter the study (subjects with more than 3 lesions are not excluded from the study, however 3 target lesions are determined for study evaluation only.)
4. Subjects able and willing to comply with the requirements of the study
5. Age  $\geq 18$  years
6. Informed Consent signed by the subject consenting to undergo the study
7. Lesions up to 8cm^2
8. Lesions with a depth up to 3mm confirmed on biopsy report AND deemed appropriate clinically by treating clinician
9. Subjects who are not deemed suitable for surgery, for example due to tumour location, performance status or other comorbidities as deemed relevant by the treating clinician
10. Patients who may have declined Surgery and/or fractionated Radiation Therapy

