## 7.3 Withdrawal and Discontinuation

### 7.3.1 Subject Withdrawal

In general, subjects should not be withdrawn prior to completion of the study.

However, subjects who withdraw consent to participate must be withdrawn from the study. No justification for such a decision is required. If a subject withdraws from the study, the investigator must be informed immediately. If the subject has already received the investigational treatment prior to withdrawal of consent, he/she will be offered to return for a safety follow-up visit. No data obtained after withdrawal of consent will be recorded on case report forms and will not be evaluated as part of the clinical study.

Subjects must be withdrawn if:

- The investigator decides it in the best interest of the subjects, i.e., any situation in which, in the investigator's opinion, a continuation of the treatment with the study medication would be harmful to the subject's safety and well-being.
- The subject is retreated for the same lesion with another therapy or device (other than Rhenium-SCT)

- The subject requires retreatment with Rhenium-SCT

Further reason for withdrawal could be:

- Serious adverse event (SAE) considered to be related to treatment with the investigational medicinal product

In all cases the date, circumstances and any reason provided will be documented on the withdrawal page of the eCRF and in the subject's medical records.

The sponsor reserves the right to request the withdrawal of a subject due to protocol deviation(s), administrative or any other valid and ethical reason(s).

Subjects withdrawn from the study will be informed about the reasons for their withdrawal.

In any case, if possible, a final study examination should be performed on subjects who discontinue prematurely. This examination should include all procedures performed at the end of treatment visit. All ongoing AEs/SAEs of withdrawn subjects have to be followed up until no more signs and symptoms are verifiable or the subject is in stable condition.

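### Four sections give different triggers for removing a whole subject, so one lesion can end the 12- and 24-month assessment of that subject's other target lesions although the endpoint counts lesions

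*Protocol*

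**What the plan says.** The synopsis gives the primary endpoint as "The number and percentage of lesions achieving CR during the study", and section 5.2 repeats it. Section 11.7 analyses it as best overall response per lesion and also tabulates lesion response at each timepoint; the synopsis lists these as 6, 12 and 24 months. Section 9.2.1 and the synopsis place the complete response (CR) rate at 12 months.

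Inclusion criterion 3 in section 7.1 adds that "subjects with more than 3 lesions are not excluded from the study" and that "3 target lesions are determined for study evaluation only". A subject may therefore have up to three target lesions, and others besides.

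The exit rules all apply to the subject:

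- Section 6.1: "Subjects requiring further or alternative treatments for the target lesions during the trial period, will leave the study".
- Section 7.3.1, two bullets among the mandatory reasons: "The subject is retreated for the same lesion with another therapy or device (other than Rhenium-SCT", and "The subject requires retreatment with Rhenium-SCT". The second names no lesion. Progressive disease (PD) is not listed.
- Section 9.1.4: the subject leaves if "they require alternative or further treatments for their lesions; or" if PD is found.
- Section 9.2.1: a PD assessment leads to withdrawal.

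The response criteria in Appendix 5 define PD by growth in the sum of target-lesion diameters or by any new lesion, with no limit on site. Table 4 in the same appendix counts new lesions at treated sites only. A closing examination is to be done where possible (7.3.1), or the investigator is to try to arrange it (9.1.4). Section 11.11 uses all available data and imputes nothing.

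**The concern.** The unit of exit is the subject and the unit of the endpoint is the lesion. When a subject leaves because of one lesion, the other target lesions lose whatever 12- and 24-month assessments remain, although nothing happened to them. No analysis plan can recover assessments that were never made. Only subjects with several lesions are affected.

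The four sections also disagree on what triggers exit: a need for treatment or treatment already given, target lesions or any lesion, PD included or not. Sites that follow different sections would keep or remove the same subject, so the set of lesions with 12- and 24-month data would depend partly on which page was read.

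**Working it through.** **Side-by-side reading.** Leaving aside the investigator's general discretion in 7.3.1:

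| Situation | 6.1 | 7.3.1 | 9.1.4 | 9.2.1 |
|---|---|---|---|---|
| One target lesion needs another therapy, not yet given | leaves | not listed until given | leaves | silent |
| A non-target lesion needs another therapy, all targets clear | stays | unclear which lesion is meant | leaves on the unqualified wording | silent |
| A non-target lesion needs Rhenium-SCT again | stays | leaves on the unqualified wording | leaves on the unqualified wording | silent |
| New lesion away from treated sites | silent | not listed | PD by the Appendix 5 criteria, not by Table 4 | same |
| One target lesion in partial response or stable disease, no treatment needed | stays | stays | stays | stays |

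The first four rows show conflict or ambiguity. The last shows that incomplete response alone is not a trigger.

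**Growth PD.** Appendix 5 uses the sum of diameters. Take three lesions of 2 cm, one growing by 20% and two unchanged: (2.4 + 2 + 2 − 6)/6 = 6.7%, below the 20% limit. One growing lesion therefore need not end participation. It can do so once the others have cleared, because the reference is the smallest sum recorded and the sum is then that one lesion. The synopsis definition allows either the lesion or the sum.

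**The plan's own figures.** The protocol gives no figure for this loss. Its sample size does reproduce: for 120 subjects and one-sided alpha 0.025, an exact binomial test gives power of 89.3%, 81.6%, 85.3%, 89.1%, 93.0% and 84.7% for the six rows of Table 3. That calculation assumes one lesion per subject, so the loss described here is zero in it by construction.

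**Size of the loss.** Let q be the chance that a lesion triggers exit before the later visits, independent between lesions. In a subject with k target lesions, a responding lesion loses later follow-up with probability 1 − (1 − q)^(k−1). The protocol does not give q; the values below are assumptions.

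| q | k = 1 | k = 2 | k = 3 |
|---|---|---|---|
| 3% | 0 | 3% | 5.9% |
| 5% | 0 | 5% | 1 − 0.95² = 9.8% |
| 6% | 0 | 6% | 11.6% |
| 10% | 0 | 10% | 19.0% |
| 15% | 0 | 15% | 27.8% |

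**Study-wide.** This needs the share of multi-lesion subjects, which the protocol also does not give.

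- The one lesions-per-patient figure in the document (section 4.3) is 55 lesions in 52 patients, so 3 lesions are additional. If three patients had two each, 6 of 55 lesions shared a patient, and the loss at q = 5% is 6/55 × 0.05 = 0.5%. If instead one patient had three and one had two, it is (3 × 0.0975 + 2 × 0.05)/55 = 0.7%.
- With an assumed 70/20/10% of 120 subjects having one, two or three lesions (168 lesions) and q = 6%: 120 × (0.2 × 2 × 0.94 × 0.06 + 0.1 × 3 × 0.94 × 0.1164) = 6.6 responding lesions, or 4.0% of all lesions.
- With 50/30/20% (204 lesions) and q = 6%, the same formula gives 11.9 lesions, or 5.8%.

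**The case against.** The strongest reply is that exit by subject is a defensible choice. The quality-of-life questionnaire in Appendix 2 concerns the subject, and the cosmetic scale in Appendix 3 asks one question covering all treated lesions, so data collected after another therapy would be mixed. This stands as a cost of the change, but it does not resolve the conflict between sections.

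Second, the wording in 9.1.4 can be read with 6.1 as meaning target lesions, and section 8.1.7 states that no therapy is prohibited in follow-up. That is a reasonable reading. Exit through a non-target lesion is therefore a possible result of unqualified wording, not a settled rule.

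Third, several stronger readings are tempting, and the document does not support them:

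- A reader might infer that any failing target lesion removes the subject. Tables 4 and 5 carry partial response and stable disease forward.
- A reader might take the 82% response after a single application in section 4.3 as an 18% exit chance, giving 1 − 0.82³ = 45% of three-lesion subjects with a failing lesion and 1 − 0.82² = 33% of their responding lesions affected. Non-response is not exit, the 82% is not clearly a lesion-level rate, another series in that section reports remission of all lesions, and section 11.1 expects CR close to 100%.
- A reader might say that existing data are thrown away. Section 11.11 uses all available data, and CR seen at 6 months or at an exit visit still counts as best overall response.
- A reader might conclude that durability will look better than it is. Under the independence assumed above, the loss costs precision only. Bias needs lesions within a subject to respond alike, which the document does not quantify, and durability is not a listed endpoint.

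**Conclusion.** The concern holds in a limited form. Sections 6.1, 7.3.1, 9.1.4 and 9.2.1 state different subject-level exit triggers, and Appendix 5 disagrees with its own Table 4 on new lesions. A treatment trigger or new-lesion PD arising from one lesion ends the later assessment of the subject's other target lesions, while the endpoint is per lesion.

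The harm falls on the 12-month CR rate and the 24-month data. Best overall response is largely protected by earlier assessments, except where CR would first have been seen after exit.

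The size cannot be fixed from the document. At an assumed 5% exit chance per lesion with independence, it is 5% of responding lesions in two-lesion subjects and about 10% in three-lesion subjects. Study-wide it is about 0.5% if lesions per patient resemble the cited series, and several percent if multi-lesion subjects are common. The contradiction needs correcting whichever applies, because sites cannot follow all four sections at once.

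**What to change.** Reconcile sections 6.1, 7.3.1, 9.1.4 and 9.2.1 and the new-lesion wording in Appendix 5 with each other and with the lesion-level endpoint. The text should settle whether need or receipt of treatment is meant, which lesions count, whether PD is a trigger, and where a new lesion must lie. Which clinical rule is right is not judged here.

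As a data-collection matter only, and without bearing on the care any lesion receives:

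- record the response status of each target lesion at the time of any exit trigger;
- continue the 12- and 24-month response assessments already scheduled for unaffected target lesions in subjects who consent.

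The cost is an amendment to four sections and one appendix and a lesion-status field in the eCRF; the visits are already in the schedule. The downside is that quality-of-life and cosmetic scores collected after another therapy must be flagged or excluded from those analyses.

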## 9.2 Efficacy Assessments

### 9.2.1 Response Assessments

The rate of Complete Response (CR) for subjects treated with Rhenium-SCT will be calculated at 12 months post-therapy.

An interim analysis is planned once 50% of the subjects have had their 6-month Follow-Up visit.

Treatment responses will be assessed according to the MODIFIED VISUAL RECIST at Baseline and during the Treatment and Follow-Up phases. If an assessment during the study results in Progressive Disease (PD) according to MODIFIED VISUAL RECIST, subjects will be withdrawn and further treated off study.

### 9.2.2 Trial App

The trial will have an associated App, available for Apple and Android smart phones, through which the following data will be collected (and will be directly populated into the eCRF):

- QoL questionnaire prior to treatment: (anytime during the screening period, after consent has been given and the subject has been enrolled into the study) and at the 6-, 12- and 24-month Follow-Up visits
- Comfort of Treatment: recorded within 14 days post-therapy with Rhenium-SCT
- Subject rated Cosmetic Outcome: recorded at 12 months and then at 24 months
- Monthly photos for general visual assessment from the 14-day post-therapy visit onwards

The app will be made available in English and German, the language can be selected and changed within the app itself.

The App is available for subjects who have a smart phone with a camera function. **Subjects who do not have a smart phone can still enter the study but will need to complete assessments as follows:**

- Instead of the subject taking photos on a smart phone App monthly, the site staff will take photos at the Follow-up visits and upload the images into the eCRF
- Comfort of treatment will be recorded by the subject via short paper questionnaire at the Day 14 post-therapy visit - and then entered by site staff into the eCRF
- QOL is to be completed by the subject on paper questionnaire and then entered into the eCRF by the site staff at the Follow-up visits. This will be done during the Baseline visit, then at the 6 and 12 month Follow-up visits
- Cosmetic Outcome - subject rated. This is to be entered into the eCRF. The subject will verbalise the response having seen a copy of the VAS scale (in protocol appendix 3) This will be completed at the 12- and 24-month Follow-up visits

Upon enrolment into the study, and once informed consent has been gained, the eCRF will generate a unique App code for the subject.

The subject will download the trial App from the Apple Store or Google Play and enter this unique code in order to access the App and its functionality.

No data recorded via the App is stored on the phone for privacy compliance. All data is immediately transferred from the App to the eCRF or a secure server.

Photos taken by the subject via the Trial App should be:

- The subject may need the assistance of a family member or friend to take the photos if the target lesions are difficult to reach.
- Two separate photos of each target lesion are to be taken: one in indoor light, and one in natural light. The App will prompt the subject accordingly.

The App will deliver pop-up notifications to the subject's smart phone at timepoints where subject reporting is required.

Photos are to be evaluated by the principal investigator (PI) or allocated study nurse. No scoring or assessment is required from the App photos but are to be utilised for general assessment. At the end of study, the App photos may be utilised to assess the lesion over time, in general terms.

At sites where a medical photographer or photography equipment is available, the photos can be taken in this way at Follow-up visits and uploaded directly to the eCRF.

### **9.2.3 Subject Reported Outcome Measures (PROMs)**

Via the trial App (or at follow-up visits for subjects with no smart phone), the following will be recorded:

- QoL questionnaires
- Subject reported Cosmetic Outcome
- Comfort of Treatment

In addition:

- Monthly photos of treated lesions are taken for general assessment by the site

## **9.3 Demographics and Medical History**

Demographic data to be collected for this study include:

- Gender
- Age
- Ethnicity
- Fitzpatrick score (Fitzpatrick Classification Scale for Skin Types)

The medical history comprises:

- All relevant medical conditions/illnesses in the past and present at the start of the study.

## **9.4 Safety Assessments**

### **9.4.1 Clinical Laboratory Evaluation**

No clinical laboratory evaluations are planned for the study (Rhenium-SCT is administered by application on a protective foil applied over the area to be treated, such that the radioactive material does not come into contact with the subject).

It is noted that histology is to be taken during the screening period to confirm type of lesion as well as depth of lesion.

